### Inclusion and exclusion criteria

2.3

Although children in many research studies are defined as <18 or <21 years of age, in practice, children with severe epilepsies such as LGS often remain with their pediatric providers well into their third decade of life, because of severe disability, and may continue to have coverage up to age 26 through their parents’ health insurance plans. Patients in the cohort will have been less-than-or-equal-to 26 years old at the beginning of the study period.

Inclusion and exclusion criteria for Aims 1a, 1b, and 2 are shown in Table 1.

**Table 1 tab1:** Study inclusion and exclusion criteria.

Aims	Inclusion criteria	Exclusion criteria
Aim 1a	Patient has a validated diagnosis of LGS or meets one of the LGS computable phenotype definitions the study evaluated Index treatment occurred between 2016 and 2021: first epilepsy surgery or initiation of additional LGS-approved medication Patient received neurological care at a study site at least 1 year before intervention and 2 years after intervention at the site	Patient does not meet minimum follow up criteria for neurological care at the study site
Aim 1b	Patient has a validated diagnosis of LGS Patient is currently being treated at a study site Caregiver can participate in English or Spanish	
Aim 2	Computable phenotype for LGS based on Aim 1a	

LGS, Lennox–Gastaut syndrome.

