### Study aims

2.1

Aim 1: Determine the effect of epilepsy surgery and LGS-approved anti-seizure medications on two key clinical outcomes in children with LGS.

a. Compare the effectiveness of the addition of surgeries versus the addition of another medication for reducing seizure-related emergency healthcare utilization.

b. Compare the effectiveness of these two pathways and of early versus later use of surgery versus medications on measures of children’s expressive communication, behavior, and quality of life.

Aim 2: For individuals with LGS, describe real-world utilization of these treatments across multiple centers in the US, and identify variability including disparities that may currently pose challenges and barriers to ensuring optimum access to and use of appropriate therapies.

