### Study design

2.2

This multicenter, mixed-methods comparative effectiveness study will use the Patient-Centered Clinical Research Network (PCORnet®) data mart infrastructure to work with 18 academic pediatric sites across 5 clinical research networks: PEDSnet, a national pediatric learning health system; PaTH Towards a Learning Health System (PaTH); Stakeholders, Technology, and Research (STAR); OneFlorida+; and Greater Plains Collaborative. PCORnet® is a national research network of health systems with access to electronic health records (EHR) data that have been standardized using a common data model (35). The 18 PCORnet® sites we selected have large clinical programs in pediatric epilepsy and serve large numbers of patients with LGS. At 7 high-intensity sites, clinical research teams will conduct EHR review for coding validation of the diagnosis of LGS and will recruit caregivers to complete surveys measuring communication, behavior, and quality of life. Computable phenotypes for LGS will be developed based on elements available in the EHR. Data from an additional 11 sites (light-touch sites) will be pulled and analyzed based on cohort identification by these computable phenotypes (Figure 1).

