**Figure 2 fig2:**
[figure not shown]
LGS classification workflow in Aim 1a. CRCs, clinical research coordinators; EHR, electronic health record; LGS, Lennox–Gastaut syndrome.

Data on emergency healthcare utilization, as well as treatments and covariates, will be extracted from PCORnet® data marts of the 7 high-intensity sites. The data types include demographics, diagnoses and conditions, encounters, procedures, prescriptions, medication administrations, healthcare providers, and deaths. Seizure-related emergency healthcare utilization will be defined as the frequency per year of seizure-related ED visits and seizure-related inpatient admissions in the 2 years after intervention (surgery or medical), with adjustment for the rate during the year before intervention. A secondary analysis will be done for 1 year after intervention as well. The index date of the intervention will be defined between January 1, 2016, and December 31, 2021, as that of the first relevant surgery or (if there was no surgery) that of the first exposure to a third anti-seizure medication, with at least one of the three being among the seven LGS-approved medications listed above. To the extent possible, we will also control for dietary therapy as a variable collected by chart review and accessible by codes. We also will analyze all emergency healthcare visits and inpatient visits (with or without seizure diagnosis codes) and the subset for which there is a diagnosis of fracture, head trauma, lacerations/avulsions/contusions, burns, aspiration, aspiration pneumonia, or near drowning (37), as an expanded seizure-related definition. Subset analysis will be done on data from 2020 and 2021, the years of the COVID-19 pandemic (38).

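### Aim 1a counts emergency care only in the seven sites' own data marts, so any arm difference in care received elsewhere biases the rate ratio; separately, the age cap is anchored at study start rather than at index

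*Protocol article*

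**What the plan says.** **Outcome source.** Data collection, Aim 1a (2.4.1) states: "Data on emergency healthcare utilization, as well as treatments and covariates, will be extracted from PCORnet® data marts of the 7 high-intensity sites". In the same section, "Seizure-related emergency healthcare utilization will be defined as the frequency per year of seizure-related ED visits" and admissions over the 2 years after intervention, adjusted for the rate in the year before. Study design (2.2) describes "18 academic pediatric sites across 5 clinical research networks", of which these seven are a subset, and describes the network as offering "access to electronic health records (EHR) data that have been standardized using a common data model". No claims linkage, record exchange with other hospitals, or caregiver report of outside visits is described for this outcome.

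**Capture rule.** Table 1 requires neurological care at the study site for at least 1 year before and 2 years after the intervention. It sets no condition on where emergency care is received.

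**Age rule.** Inclusion and exclusion criteria (2.3) states: "Patients in the cohort will have been less-than-or-equal-to 26 years old at the beginning of the study period". The reasons given are that patients with severe epilepsy often stay with pediatric providers into their third decade and "may continue to have coverage up to age 26" through a parent's plan. The study period starts in 2016, and index dates run from 1 January 2016 to 31 December 2021. Study aims (2.1) frames Aim 1 as: "Determine the effect of epilepsy surgery and LGS-approved anti-seizure medications on two key clinical outcomes in children with LGS".

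**The concern.** Attending neurology clinic at a referral center does not mean taking a prolonged seizure to that center's emergency department. A family living at a distance may meet every Table 1 criterion and use a nearer hospital in an emergency. Those visits are not recorded as missing; they are simply absent from the count. The comparison is not randomized, so nothing in the design makes the share of unseen visits equal in the surgery and medication arms. If it is unequal, the Aim 1a rate ratio partly measures where patients go for emergency care.

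The age rule is a separate, smaller matter. Its reasons concern a patient's situation around age 26, but the limit is checked in 2016 and not when the patient is treated and followed. Some patients can therefore be counted at ages where those reasons no longer apply and emergency care may be given at adult hospitals.

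**Working it through.** The article states no event rate, effect size, power or capture share for Aim 1a, so it has no figure of its own to reproduce.

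**1. Age, from the stated dates**
- Aged 26 on 1 January 2016, indexed on 31 December 2021: 26 + 6 = about 32 at index (just under 33 if 26 means completed years).
- The 2-year outcome window from that date would end at about 34, but it would run to the end of 2023. The stated study period ends in 2022, and an extension of the data is described only under Aim 2. Within data to the end of 2022, a full 2-year window needs index by 31 December 2020: about 31 at index and 33 at the end.
- With the limit applied at index: at most about 26 + 2 = 28 at the end of follow-up (just under 29 for completed years).

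**2. Capture bias, by formula**

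Let c be the share of emergency events seen in the site's data mart (assumed), with a true rate ratio of 1.
- Unadjusted ratio = c(surgery, after) / c(medication, after).
- Ratio of ratios = [c(surgery, after) / c(surgery, before)] / [c(medication, after) / c(medication, before)].

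| Assumed capture | Unadjusted | Ratio of ratios |
|---|---|---|
| 0.8 in both arms and periods | 1.00 | 1.00 |
| surgery 0.6, medication 0.8, both periods | 0.6/0.8 = 0.75 | 1.00 |
| surgery 0.8, medication 0.6, both periods | 0.8/0.6 = 1.33 | 1.00 |
| 0.7 in both before; surgery 0.8, medication 0.7 after | 0.8/0.7 = 1.14 | 1.14 |

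**3. Prior-year count as a covariate, by simulation**

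Poisson regression with no true effect and one third in the surgery arm (the article's expectation). Patient rates are gamma-distributed, with assumed mean 1 per year and shape 0.8. There is 1 year of counts before index and 2 years after, both thinned by the capture share. Thinning was either uniform or by patient (user or non-user of the site), and the prior count entered either as is or as log(1 + count).
- Equal capture: about 1.00.
- Surgery 60%, medication 80%: about 0.75 unadjusted, about 0.83 to 0.88 adjusted.
- Surgery 80%, medication 60%: about 1.33 unadjusted, about 1.13 to 1.23 adjusted.
- Surgery 70%, medication 80%: about 0.88 unadjusted, 0.93 to 0.96 adjusted.
- A difference arising only after index (last row of the table; run with mean 1.5 and shape 1): about 1.14 adjusted, so essentially nothing is removed.

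One year's observed count is a noisy measure of a patient's rate, so conditioning on it corrects a constant difference only in part. The ends of these ranges move by a few hundredths with the assumed event rate and the simulation run.

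**4. Would a restricted analysis help?** In the 60% v 80% case, restricting to local users by a flag unrelated to the surgical work-up brings the ratio back to about 0.97 to 0.99. The definition matters. A looser flag, such as any outpatient visit that is neither neurology nor a procedure, would be met by a pre-operative neurosurgery clinic visit. If every surgical patient is flagged in that way, then even with equal 70% capture the restricted ratio falls to about 0.70 unadjusted and 0.79 to 0.85 adjusted. That is a false effect where the full analysis has none.

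**The case against.** The bias is conditional. It needs capture to differ by arm, and the article gives no capture share, catchment area or referral pattern. This stands: the size and direction are assumptions, and equal loss is harmless to the ratio.

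The plan has safeguards. Requiring neurology care at the site before and after the intervention removes one-off surgical referrals. The prior-year rate comes from the same source, and if that adjustment were made as a ratio of ratios, a constant capture difference would cancel. The propensity covariates are given as examples, so a place-of-care variable is not ruled out, and a data mart may cover more of a health system than one hospital. These points reduce the concern but do not close it. The continuity rule concerns neurology rather than emergency visits, a covariate adjustment leaves roughly half of a constant difference, and no form of prior-year adjustment removes one that arises after index. The limitations section mentions incomplete historical data only in general terms.

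Two stronger readings are tempting. A reader might infer that the result will favor surgery, on the view that surgical patients come from further away. The article says nothing about this, and the opposite pattern gives a bias of similar size against surgery. A reader might also infer that the age anchor produces a false treatment effect. It does not: it applies equally to both arms, the oldest patients count only if still in neurology care at the site, and age is in the propensity model. Nor is including patients over 18 a departure in itself, since section 2.3 explains it.

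Sensitivity analyses are often left to the analysis plan. But the data source, the capture rule and the age anchor are fixed in this article.

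**Conclusion.** The concern holds as a conditional one. Aim 1a emergency use is ascertained only in the sites' data marts, and continuity of neurology care is the only condition that bears on capture. If the share of emergencies treated elsewhere differs between arms, the rate ratio is biased and prior-year adjustment removes only part of it. With assumed capture of 60% v 80% and no true effect, the adjusted ratio is about 0.83 to 0.88, or about 1.13 to 1.23 with the arms reversed; with equal capture it is 1.00. The article establishes neither that a difference exists nor which way it runs.

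The age anchor is a distinct inconsistency between the rule and its stated reasons. It admits patients up to about 32 at index, may add to under-capture, and does not itself create an arm difference. Both points are worth correcting because the outcome is central and the changes are cheap.

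**What to change.** 1. In section 2.3, apply the age limit at the index date.
2. In section 2.6.1, prespecify a sensitivity analysis of the Aim 1a primary comparison restricted to patients who use the site's system for general care. Define this in the pre-index year, identically for both arms, by encounters unrelated to epilepsy or the surgical work-up: for example primary care or general pediatrics, excluding neurology, neurosurgery, pre-operative and procedural visits. Report the share of such patients by arm.
3. Report the restricted estimate beside the primary one. If they disagree, let that limit the conclusion; do not switch to the restricted estimate after seeing the results.

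**Cost.** Wording, plus programming on encounter data that are already to be extracted. The oldest patients are lost, and the restricted analysis will have wider intervals.

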## Introduction

1

Lennox–Gastaut Syndrome (LGS) is a severe developmental epileptic encephalopathy that affects an estimated 48,000 children and adults in the United States (US) (1). LGS is characterized by multiple seizure types, life-long treatment resistant seizures, developmental delay, cognitive and behavioral impairments, and early death (2–4). The onset of seizures is typically in the first 2 years of life, but the syndrome is often not fully recognizable until children are 3 to 5 years old (2, 5). Individuals with LGS have multiple types of seizures including tonic–clonic, tonic, and atonic seizures (2). Prolonged seizures are common and require the use of rescue medications, emergency department (ED) visits, and unplanned hospital admissions (6, 7).

LGS, although rare, accounts for a disproportionate amount of healthcare utilization and expenditures. It accounts for up to 10% of all childhood-onset epilepsies and 1–2% of all epilepsies; however, it represents one-fifth or more of treatment resistant pediatric epilepsy (2, 8–10). Among children and adults, expenditures are two or more times greater in association with LGS than with other forms of epilepsy (11), and all-cause mortality in young people with LGS is ten times that in the general population (3). In a survey about living with LGS, 75% of parents reported that their child experienced seizures every day in the prior week, 30% reported going to an ED at least once in the past 6 months, and 51% reported using rescue medication to stop a seizure in the past 6 months (7). In addition to the burdens created by seizures, people with LGS have a profound level of cognitive and physical impairment. A caregiver-driven survey of young people with severe epilepsies found that in the subgroup with LGS, 42% did not walk independently, 25% did not have functional hand grasp, 42% were entirely dependent on someone else for feeding, 55% did not effectively communicate, and 50% were nonverbal (4). This degree of impairment further increases medical burden and financial stress with hidden costs of care, and significantly impacts the quality of life of patients with LGS and their families (12, 13).

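### Aim 1a entry requires 2 years of site care after treatment, the same 2 years in which the outcome is measured, so early deaths and departures drop out of the comparison

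*Protocol article*

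**What the plan says.** Section 2.3, Table 1, sets this inclusion criterion for Aim 1a: "Patient received neurological care at a study site at least 1 year before intervention and 2 years after intervention at the site". The only exclusion listed for Aim 1a is its mirror image: "Patient does not meet minimum follow up criteria for neurological care at the study site". No exception for death or transfer is stated.

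Section 2.4.1 defines the outcome as a yearly frequency of seizure-related emergency department visits and "seizure-related inpatient admissions in the 2 years after intervention (surgery or medical), with adjustment for the rate during the year before intervention". It adds: "A secondary analysis will be done for 1 year after intervention as well". No separate entry rule is given for that shorter window.

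On dates, Section 2.4.1 states: "The index date of the intervention will be defined between January 1, 2016, and December 31, 2021". The same section gives the retrospective study period as 2016 through 2022.

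The data types to be extracted include "prescriptions, medication administrations, healthcare providers, and deaths", but the article gives deaths no stated role in the analysis. The Introduction reports that "all-cause mortality in young people with LGS is ten times that in the general population".

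Section 2.6.1 handles confounding by inverse probability of treatment weighting, with a treatment model built on what is known at the time of the decision. Section 3.4 acknowledges selection bias only from patients joining the open cohort at different times.

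**The concern.** Eligibility should be decidable on the index date. Here it depends on what happens over the next 2 years, which is the period in which outcome events are counted. Someone who dies or moves to another provider at month 8 has 8 months of relevant experience after treatment, and the rule discards all of it.

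Two things are at stake. The first is the rate ratio: if surgical and medication patients are lost at different rates, or those lost differ in event rate in a different way by arm, the retained groups are no longer comparable, even if the treatment weights are perfect. The second is mortality: in a population with the excess mortality that the article itself cites, deaths in the first 2 years would not be visible in the comparison, although the data are being extracted.

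The 1-year analysis appears to inherit the same restriction. A patient observed for the whole first year but not the second would not contribute to it.

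**Working it through.** **No figure of the plan to reproduce.** The article gives no retention, event rate, absolute mortality, power or effect size for Aim 1a. What follows is a reading of the rule, a date check that uses the plan's own dates, and an illustration with assumed inputs.

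**1. Entry rule against outcome window.** Entry needs site care through 2 years after the intervention (Table 1). The outcome is counted from the intervention to 2 years (Section 2.4.1). The two periods coincide. The treatment model in Section 2.6.1 uses decision-time information, so it balances who received which treatment, not who remained. Section 2.6.1 also mentions a 6-month comparison and 1-year rate ratios. Those windows lie inside the 2 years, so the same selection applies to them unless another entry rule is set.

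**2. Date check.**
- Index window, 1 January 2016 to 31 December 2021: 6 × 365 + 2 leap days = 2,192 days.
- If data end on 31 December 2022, an index date of 1 January 2021 has just under 2 years of follow-up, and one of 31 December 2021 has about 1.0 year.
- All 365 index days in 2021 therefore fall short: 365 / 2,192 = 16.7% of the window. This is a share of calendar time, not of patients.

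**3. Illustration of bias.** Let d_S and d_M be the shares excluded in the surgery and medication arms, and let excluded patients have r times the event rate of retained patients in the same arm. The full-arm rate equals the retained rate × (1 − d + d·r). If the true rate ratio (surgery/medication) is 1.00, the ratio among retained patients is

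(1 − d_M + d_M·r) / (1 − d_S + d_S·r).

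All values of d and r below are assumptions.

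| d_S | d_M | r | Calculation | Ratio seen |
|---|---|---|---|---|
| 15% | 5% | 2 | 1.05 / 1.15 | 0.913 |
| 10% | 5% | 2 | 1.05 / 1.10 | 0.955 |
| 10% | 5% | 0.5 | 0.975 / 0.95 | 1.026 |
| 15% | 5% | 0.5 | 0.975 / 0.925 | 1.054 |
| 5% | 15% | 2 | 1.15 / 1.05 | 1.095 |
| 10% | 10% | 2 | 1.10 / 1.10 | 1.000 |

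More extreme assumptions (30% against 10% in either direction, r = 3) give 1.20 / 1.60 = 0.75 and 1.60 / 1.20 = 1.33. The formula weights each patient equally and ignores the shorter time at risk of those who leave. It shows how the bias arises and is not an estimate of its size.

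**The case against.** The rule has a purpose. Outcomes come from the sites' own data marts. Once a patient's care moves elsewhere, events at other hospitals may be unseen and counted as none, so requiring continued site care protects ascertainment. This stands, and any replacement must deal with it. It also rules out a careless fix: censoring at the last encounter of any type would let an emergency visit or admission set the end of person-time, tying the denominator to the outcome.

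The usual explanations for unequal loss are only partly supported. Patients referred solely for surgery and then returned to local care are largely screened out by the requirement of a year of site care beforehand, which applies to both arms. Ageing out is weakened by Section 2.3, which says that such patients often stay with pediatric providers well into their twenties. That medication failures seek care elsewhere has no source in the article.

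How the rule will operate is also uncertain. An index cut-off one year before data end suits a 1-year minimum, and Section 2.4.3 uses that logic, though only for Aim 2. The article does not say in words that deaths are removed, or that the 1-year analysis is confined to patients retained for 2 years; both follow from reading Table 1 literally.

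Finally, offsets, censoring rules and the handling of death are often left to a full protocol or analysis plan, so their absence from an article is not the point. The eligibility criterion, however, is stated here, and an analysis plan that follows it cannot recover patients who never enter the cohort.

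**Conclusion.** The point holds as a flaw in a stated eligibility rule. Read literally, Table 1 conditions entry on survival and retention through the outcome window, and the planned weighting cannot undo this. Index dates in 2021, 16.7% of the window, cannot satisfy the rule if data end in 2022.

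A reader might infer that the comparison is certainly biased, or biased in favour of one arm. The documents do not support that. The mortality figure is relative, with no absolute rate and no split by arm, and loss by arm is not given. If exclusion and its link to event rate are the same in both arms, a null ratio stays at 1.00. The range of about 0.91 to 1.05 rests on assumed exclusions of 15% or 10% in the surgery arm against 5% in the medication arm and relative event rates of 2 or 0.5; reversing the arms reverses the direction.

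Even with equal selection, the results would describe only patients who survive and stay at the site for 2 years, and early deaths by arm would not be seen.

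**What to change.** - **Entry.** Define Aim 1a eligibility by pre-index criteria only, keeping the 1-year lookback at the site.
- **Follow-up.** Follow each patient from index to the earliest of 2 years, death, end of site care or data end, with log person-time as offset. This fits the planned Poisson log-link model directly.
- **End of site care.** Date it by a rule that does not depend on the outcome, for example the last routine neurology contact plus a fixed grace period, and not by the last encounter of any type.
- **Deaths.** Report deaths by arm from the data already being extracted.
- **Supporting analyses.** Use inverse-probability-of-censoring weights as a supporting analysis, since loss may be informative. Keep the 2-year completers as a sensitivity analysis, so nothing now planned is lost.
- **Dates and windows.** Reconcile the 2-year rule with the 2016–2021 index window and the data end, and state which entry rule applies to the 1-year analysis. With censored person-time, patients indexed in 2021 can contribute their 1 to 2 years.

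Cost: a change to a protocol eligibility criterion, matching analysis-plan wording and modest programming. No new data types are needed. The price is some loss of certainty about events at other hospitals near the end of site care; the completers' sensitivity analysis shows how much this matters.
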